**Methods:**

This trial is a parallel two-arm randomized clinical trial, which includes both process (i.e., feasibility and acceptability) and efficacy evaluation (i.e., change in primary and secondary outcomes and moderated effects) of Tuning in to Kids^®^ in Portugal. A minimum of 152 parents/legal guardians (> 18 years old) with at least one child between 3 and 6 years old will be enrolled. Parents will be randomly assigned to the intervention group or waiting list control group (76 per condition), through blocked randomization, with allocation concealment. Participants in both conditions will complete self-report questionnaires assessing primary (parental emotion socialization) and secondary (parents and children functioning dimensions) outcomes at baseline, post-intervention, and follow-up (2 months post-intervention). Longitudinal data will be analyzed using linear mixed-effects models accounting for repeated measures within participants.

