### Participants

Eligible participants will be parents/legal guardians (hereafter referred to as “parents”) (1) with at least one child aged between 3 and 6 years old (inclusive) who lives with the parent, (2) at least 18 years old, (3) who can read, understand, and speak Portuguese, and (4) who live in the Lisbon Metropolitan Area or Lisbon District. When requested, both parents will be allowed to participate. Exclusion criteria include (1) parents’ being currently enrolled in another structured parenting program, (2) the child is already attending elementary school at the time of recruitment, (3) the child has a diagnosis of a severe Communication and/or Developmental Disorder, or (4) the child is under a child protection measure that implies that the child does not live with their parents (e.g., if the child is in foster care). Parents who have multiple children within the target age range will be instructed to respond with reference to the child for whom they experienced the most concern.

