### Randomization and blinding

To ensure balanced groups throughout the enrollment period, randomization will be conducted using a permuted block procedure, with block sizes varying between 4 and 6, depending on the number of eligible parents. To ensure allocation concealment, the sequence will be generated through computer randomization software by an independent researcher not involved in participants’ enrollment or assessments. Group assignments will be further communicated to the research team, who will subsequently inform parents of their allocation via telephone. Additionally, groups’ equivalence will also be assessed regarding primary outcomes and key covariates. Considering the nature of the intervention and similarly to research evaluating TIK in other countries (e.g., [48]), this study will be an open-label trial, as neither the researchers nor the parents will be blinded to the participants’ group allocation.

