#### Efficacy evaluation

The statistical analyses will be carried out using SPSS and the R software (version 4.4.0). The level of statistical significance will be set at *p* < .05. Descriptive statistics will be computed for all study variables. Pearson/Spearman correlations will be conducted to explore associations between all the study variables at each assessment wave. Pre-test differences between the intervention and control groups will be analyzed regarding sociodemographic and health characteristics (using qui-square tests) and the primary and secondary outcomes using t-tests (for dichotomous independent variables) and one-way ANOVAs (for categorical and ordinal independent variables) to identify potential covariates.

Linear mixed-effects models accounting for repeated measures within participants will be tested to analyze TIK’s efficacy. Time 0 will be defined as the date of the pre-test assessment, time 1 will be the date of the post-test, and time 2 will be the date of the follow-up assessment. Time, group conditions (intervention (coded as 1) vs. control (coded as -1)), and the 2-way interaction time x group conditions will be included in the models as fixed effects. Moreover, for children-related outcomes (i.e., children’s emotional and behavioral functioning), the child will be treated as the primary unit of analysis and models will also include a random intercept and a random slope for time at the child level in order to account for between-child variability in baseline (at pre-test) levels of the outcome variables and between-child variability in change across time. Since both parents may participate in the study, the child-level random effects also allow one to take into account the non-independence of both parents’ reports for the same child. For parents-related outcomes (i.e., parental emotion socialization and parents’ emotional and behavioral functioning), the parent will be treated as the primary unit of analysis and models will include a random intercept and a random slope for time at the parent-level to account for between-parent variability. To account for the nesting of both parents within the same family, a random intercept at the child level will be included.

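### For the primary (parent) outcomes, the only link between two parents of one child is a random intercept, which cancels from change, so the time x group test does not account for couples

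*Protocol article*

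**What the plan says.** All in the Protocol article.

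- **Who may join** (Participants): "When requested, both parents will be allowed to participate". No expected number of couples is given, and no cap.
- **Parent outcomes** (Efficacy evaluation): "models will include a random intercept and a random slope for time at the parent-level to account for between-parent variability". The family link is then added: "To account for the nesting of both parents within the same family, a random intercept at the child level will be included". The four primary measures (CCNES, PBACE, IM-P, DERS-SF) are all parent outcomes, so every primary model has this structure.
- **Child outcomes** (same section): "models will also include a random intercept and a random slope for time at the child level". The article explains that these child-level effects also deal with the two parents' reports on one child being dependent.
- **Effect tested** (same section): "the 2-way interaction time x group conditions will be included in the models as fixed effects".
- **Allocation** (Abstract, Methods): "Parents will be randomly assigned to the intervention group or waiting list control group (76 per condition), through blocked randomization". Randomization and blinding describes permuted blocks, "with block sizes varying between 4 and 6, depending on the number of eligible parents". Neither section says whether two parents of one child are allocated together.

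**The concern.** The trial's efficacy question is whether change over time differs between arms. A family intercept makes two partners alike in their general level but says nothing about whether they change together. The only random slope in the parent-outcome models is at parent level, so the model assumes that one partner's change is unrelated to the other's. Partners live with the same child and, if both are in the intervention arm, may attend the same sessions, so related change is plausible. The article says that the intercept handles the nesting of parents within a family. For level it does; for the term that carries the primary hypothesis it does not.

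At stake is the validity of the standard error, and so of the confidence interval and the 0.05 significance level, for each primary time x group test. The article already gives the child outcomes a child-level slope. The primary outcomes get the weaker structure, and no reason is stated.

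**Working it through.** **The plan's own figures.** The article gives no partner correlation, couple share or standard error, so no stated figure bears directly on this point. Its sample size of 132 for 80% power cannot be rebuilt, because neither the numeric effect nor the variances are given. Sample size does not mention clustering of partners.

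**Step 1: the intercept cancels.** Take a time contrast with weights that sum to zero, for example (-1, 0, 1) over the three visits. A family intercept adds the same constant at each visit, so its contribution to the covariance of two partners' changes is proportional to (-1 + 0 + 1)^2 = 0. Under the planned model that covariance is zero by construction.

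**Step 2: size if partners share an arm.** Let an arm hold n parents, a share c of them in couples (n x c / 2 couples), with variance of change s^2 and partner correlation of change rho. Then

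Var(mean change) = (1/n^2) x [n s^2 + 2 x (n c / 2) x rho s^2] = (s^2 / n) x (1 + c rho).

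The planned model uses s^2 / n. So true SE / model SE = sqrt(1 + c rho), and two-sided type I error = 2 x [1 - Phi(1.96 / sqrt(1 + c rho))]. Both c and rho are assumptions. The last column is what a nominal 80% power becomes once the SE is correct.

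| c | rho | 1 + c rho | SE factor | Type I error | Power |
|---|---|---|---|---|---|
| 0.1 | 0.3 | 1.03 | 1.015 | 5.4% | 79% |
| 0.2 | 0.3 | 1.06 | 1.03 | 5.7% | 78% |
| 0.4 | 0.3 | 1.12 | 1.06 | 6.4% | 75% |
| 0.4 | 0.5 | 1.20 | 1.10 | 7.4% | 73% |
| 1.0 | 0.3 | 1.30 | 1.14 | 8.6% | 69% |
| 1.0 | 0.5 | 1.50 | 1.22 | 11.0% | 63% |

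**Step 3: other allocations.** If every couple is split across arms, the covariance enters the arm difference with the opposite sign and the factor becomes sqrt(1 - c rho), below 1. If partners are allocated independently, same-arm and split couples occur about equally often and the terms cancel on average.

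**Step 4: simulation of the planned model.** Setting: 132 parents, three visits, maximum likelihood, z test, no true effect, 600 to 700 replicates (Monte Carlo SE of type I error about 1 point).

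| Parents in couples | Allocation | Correlation of true slopes | Empirical SD / model SE | Type I error |
|---|---|---|---|---|
| 40% | same arm | 0.5 | 1.03 | 7.3% |
| 90% | same arm | 0.5 | 1.13 | 9.3% |
| 90% | same arm | 0.8 | 1.13 | 7.9% |
| 90% | same arm | 0 (null check) | 1.03 | 6.3% |
| 90% | independent (two runs) | 0.5 | 0.98, 1.01 | 5.3%, 6.2% |
| 90% | opposite arms (two runs) | 0.5 | 0.93, 0.93 | 3.6%, 4.0% |

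The simulation sets the correlation of true slopes, whereas rho in Step 2 refers to observed change, which measurement error dilutes. With the simulated slope variance of 0.10 and residual variance of 0.40, and visits taken as 0, 1, 2, the residual adds 0.40 / 2 = 0.20 to the variance of an observed slope. A true-slope correlation of 0.5 is then an observed correlation of 0.05 / 0.30 = 0.17. At 40% couples the formula gives sqrt(1 + 0.4 x 0.17) = 1.03, as simulated; at 90% in opposite arms it gives sqrt(1 - 0.9 x 0.17) = 0.92, against 0.93.

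**The case against.** A reader might infer that the standard error is too small whenever both parents take part, and that type I error reaches 8% to 10%. The article does not support that.

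- **Allocation.** Understatement needs both partners in one arm. No section says so, and the wording reads as allocation of individual parents. If partners were allocated individually within the same block of 4, only 1 of the 3 remaining places would be in the first partner's arm, so a split would be more likely than not. There are hints the other way: child-outcome models take the child as the unit of analysis yet carry a group effect, which fits best if each child has one arm, and the arms are assessed on different days to limit contamination. These hints do not amount to a rule. The direction of the error cannot be read from the document.
- **Share of couples.** Joint participation is on request, which suggests a minority. Figures of 8% and above need most parents to enrol as couples.
- **Correlation.** The relevant rho is that of observed change after removing the arm-by-time effect. Values of 0.3 to 0.5 are assumptions, and measurement error pulls rho down.
- **Background.** The simulated null check already gave 6.3%, partly from maximum likelihood with a z test. With 40% in couples, 7.3% is only about one Monte Carlo SE above that.
- **The plan does recognise couples.** It includes a family term, so this is a refinement of the random-effects structure.

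All five points limit the size and direction of the error. None makes the family intercept account for nesting in the tested term: the partner covariance of change is left out under every allocation.

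**Conclusion.** The point holds in a conditional form. As a matter of algebra, the planned parent-outcome models set the covariance of partners' changes to zero, so the claim to account for nesting is not true for time x group.

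The effect on inference depends on three things that the article leaves open: whether partners share an arm, how many parents enrol as couples, and how strongly partners' changes correlate. With a shared arm, positive correlation and a minority of couples (c of 0.2 to 0.4), the SE is understated by a factor of about 1.03 to 1.10 and type I error is about 5.7% to 7.4%. With independent allocation the average bias is about nil. With opposite arms the SE is too large and the test is conservative. This is a modest problem that is cheap to correct before outcome data are analysed.

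**What to change.** 1. State in Randomization and blinding whether two parents of one child are allocated as one unit or separately.
2. For the parent outcomes, choose one of two changes in Efficacy evaluation: report the time x group term with standard errors clustered on family, or add a child-level random slope for time, as is already planned for child outcomes. Either allows for partner covariance of change however couples are allocated.
3. If the slope is chosen, name the family-clustered robust standard error in advance as the fallback for a singular fit. Only couples separate a family slope from the parent slope, so with few couples and three visits its variance will be poorly estimated. In the simulation with 90% in couples, the same arm and a true-slope correlation of 0.8, adding the slope moved the SD/SE ratio from 1.13 to 1.05 but type I error only from 7.9% to 7.4%, a change within Monte Carlo error. The robust option was not simulated.

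The cost is one model term or one robust variance step, slightly wider intervals if partners share an arm, and a possible convergence problem with the slope.

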## Methods

### Trial design

The clinical trial is registered at ClinicalTrials.gov (Identifier: NCT07350083, date assigned January 13, 2026). Ethical approval to conduct this clinical trial was obtained from the Ethics Committee of the School of Psychology and Life Sciences of Lusófona University (Ref. CEDIC-2025-10-30/CEDIC-2025-5-35). The clinical trial will be conducted in compliance with the American Psychological Association [40] guidelines and the Declaration of Helsinki [41]. The study protocol of this clinical trial follows the SPIRIT (Standard Protocol Items: Recommendations for Intervention Trials) guidelines [42] and the reporting of the RCT will followCONSORT guidelines [43].

This study is a parallel two-arm randomized controlled trial that will be conducted between December 2025 and December 2027. After completing the baseline assessment, participants will be randomly allocated to either the intervention group or the control group (allocation ratio 1:1). A wait-list group will be used to minimize threats to internal validity and because it has been considered ethically acceptable for preventive interventions [44]. Participants in the control group will receive the intervention after the follow-up assessment.

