Exploratory moderation analyses will be performed in order to examine whether pre-test psychosocial risk is a moderator of TIK’s efficacy. Psychosocial risk, the 2-way interaction time x psychosocial risk, the 2-way interaction group conditions x psychosocial risk, and the 3-way interaction time x group conditions x psychosocial risk will be added to the previous linear mixed-effects models as fixed effects. Significant interactions with the continuous predictor (i.e., psychosocial risk) will be interpreted and graphed using one standard deviation above and below the grand mean as high and low values.

All linear mixed-effects models will be estimated using maximum likelihood, and the models’ assumptions will be validated by analyzing residual graphs. Deviance difference tests will be performed between a baseline growth model with only time as a fixed effect and models with the predictors to examine model fit improvements. All models will be adjusted for the covariates identified in the preliminary analyses. One model per outcome variable will be performed. Effect size measures will be calculated, namely the ICC (intraclass correlation coefficient) for random effects and Cohen’s *f*^2^ for fixed effects, following the guidelines of Lorah [79]. These analyses, including the calculation of the effect sizes, will be performed using the package *lme4* from R.

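### Model covariates are chosen by significance tests of baseline differences between randomised arms, outcomes included, so the adjustment set depends largely on chance and the form of adjustment is left open

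*Protocol article*

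**What the plan says.** Under Efficacy evaluation, the protocol article states that "Pre-test differences between the intervention and control groups will be analyzed regarding sociodemographic and health characteristics", by chi-square tests. The primary and secondary outcomes are compared by t-tests and "one-way ANOVAs (for categorical and ordinal independent variables) to identify potential covariates". The threshold is general: "The level of statistical significance will be set at" p < .05. Later in the section comes the consequence: "All models will be adjusted for the covariates identified in the preliminary analyses". No covariates are named. Randomization and blinding adds that the groups' "equivalence will also be assessed regarding primary outcomes and key covariates", again without a list.

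The efficacy test is the interaction: "the 2-way interaction time x group conditions will be included in the models as fixed effects". For parent outcomes, "models will include a random intercept and a random slope for time at the parent-level". The text does not say whether covariates enter as main effects or also with time. It spells out interactions with time only for group and, in the exploratory moderation models, for psychosocial risk.

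**The concern.** This is a stated rule, not a detail left to a later plan. Allocation is computer-generated, concealed and made after the baseline assessment, so a significant baseline difference between arms is a chance event. It says nothing about whether the variable predicts the outcome, yet the rule admits variables on that basis and makes the primary model depend on how the randomisation happened to fall.

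Two further points follow. The screen covers the outcomes, so an outcome flagged at baseline could enter its own model as a covariate while its T0 value is already the first response. And a time-constant covariate entered as a main effect acts on the level of the outcome, whereas efficacy is judged on change. A result reported as adjusted could then suggest a correction for imbalance that did not take place.

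**Working it through.** The article gives no figure for this step, so there is none to reproduce. The checks below use its variable lists, its 5% level and its 15% attrition. The variances are not published and are assumed.

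**1. Number of tests.** Sociodemographic measures lists 13 parent items and 3 child items, giving 16. Primary outcome scores: CCNES 2, PBACE 4, IM-P 1, DERS-SF 1, giving 8. Secondary: SDQ-P 2 (or 4 with the internalising and externalising scores), ERC 2, PSS 1, HADS depression 1, MaaP 1, giving 7 to 9. The total is 31 to 33, or about 30.

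**2. Chance flags.** Expected number = k × 0.05. Probability of at least one, if independent = 1 − 0.95^k.

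| k | Expected | P(at least one) |
|---|---|---|
| 16 (background items only) | 0.80 | 56% |
| 30 | 1.50 | 79% |
| 33 | 1.65 | 82% |

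The expected number does not need independence; the probability does. Income items and subscales of one instrument are related, so the probabilities are probably too high.

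**3. Main-effect covariate, complete data.** With waves 0, 1, 2, a parent's slope is (y2 − y0)/2. A time-constant main effect adds the same amount to y0 and y2 and cancels. With groups coded 1 and −1, the time-by-group coefficient is half the difference in mean slopes, so it does not move.

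A generalised least squares check used 152 parents, 20 two-parent families, random-effect covariance [[0.5, −0.05], [−0.05, 0.06]], residual SD 0.6 and known variances. It gave 0.071302 (SE 0.03974) both with and without the covariate. With categorical time the two coefficients were 0.092887 and 0.142604, again the same either way.

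**4. What a correction would look like.** Suppose a covariate changes the outcome by 0.1 per SD per wave and the arms differ by 0.35 SD. The chance contribution to the coefficient is 0.5 × 0.35 × 0.1 = 0.0175. In 60 simulated trials fitted by maximum likelihood, the main effect moved the estimate by 0.0000 and the time-by-covariate term moved it by −0.0169 on average.

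**5. Attrition.** Shift from a main-effect covariate imbalanced by 0.35 SD, 60 simulated trials per row:

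| Scenario | Mean shift | Mean absolute shift, in SE | Largest, in SE |
|---|---|---|---|
| 15% missing completely at random | 0.0000 | 0.06 | 0.28 |
| 15% missing at random | 0.0017 | 0.08 | 0.31 |
| 15% missing at random, covariate affects change | −0.0003 | 0.09 | 0.28 |
| As above, irregular dates | −0.0005 | 0.10 | 0.30 |
| 30% missing at random, covariate affects change | −0.0005 | 0.14 | 0.41 |

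In the rows where the covariate affects change, the time-by-covariate term moved the estimate by −0.015 to −0.017 on average.

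**6. Baseline outcome as both response and covariate.** In five simulated data sets (n = 132, complete, maximum likelihood) the estimates were 0.1356, 0.1568, 0.1714, 0.0996 and 0.0945 with and without it. The SE went from about 0.039 to about 0.043 (0.043/0.039 = 1.10). A further 25 fits gave an average increase of 12% (range 7-16%). Three assumed variance sets with 12 data sets each gave about 4-16%. With the variances held fixed, as in step 3, the SE did not change. The increase therefore arises when variance components are re-estimated, as the planned maximum likelihood fit would do.

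**The case against.** The strongest reply is that the concern limits itself: if main-effect covariates leave the time-by-group estimate alone, luck in choosing them barely reaches the primary test. On that reading this is right. What remains is the SE increase when a model's own baseline outcome is admitted, and a misleading label. But if interactions with time were meant, selection does reach the primary estimate. In the complete-data simulations the time-by-covariate term moved it by 0.13 SE on average when the covariate did not affect change and by 0.41 SE when it did. Neither reading makes the rule sound.

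Other replies stand in part:

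- Entry as main effects is an inference, because the article says only that models are adjusted.
- The ANOVA clause is ambiguous. A two-arm comparison has one dichotomous factor, so ANOVAs over categorical and ordinal independent variables may relate background items to outcomes, which would select partly on prognosis. It cannot be said that prognosis is ignored altogether.
- The screen uses data collected before randomisation and a stated threshold. A reader might infer that the open-label design lets post-treatment results drive the model; the documents do not support that.
- A reader might also infer that adjustment can never move the estimate, or that it fails its declared purpose. The first is exact only for complete data at common times. The second has no basis, because no purpose is stated.

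**Conclusion.** The concern holds in this form. The stated rule selects covariates mainly on chance differences between randomised arms, about 1.5 flags expected in about 30 tests, and leaves the adjustment set unknown until baseline data are seen. If the covariates enter as main effects, they do not systematically correct the time-by-group term. Admitting a model's own baseline outcome gains nothing on complete data and costs roughly 4-16% in SE.

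The zero shift on complete data at common times is algebraic. The sizes under attrition and the SE increase depend on assumed variances. Randomisation still protects the unadjusted comparison, so this is a worthwhile improvement in the analysis wording and not a threat to the trial's validity.

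**What to change.** - Delete the between-arm tests as a selection step and report baseline characteristics descriptively by arm.
- Before analysis, fix a short covariate list on prognostic grounds from items under Sociodemographic measures, for example child age, child sex and parental education. The Introduction itself links lower parental education to less supportive emotion socialisation; the rest is the team's judgement. Recruitment site is not among the listed items. Parental education is also part of the psychosocial risk score, so its place in the moderation models should be stated.
- Use the same list in every model and enter each covariate with its interaction with time.
- Handle the baseline outcome in one way only: either a common baseline mean for both arms with T0 kept as a response, or T0 as a covariate in a model of T1 and T2 alone. The second option leaves two values per parent, so a parent-level random slope could not be separated from residual error, and the efficacy term becomes the arm difference at T1 and T2.

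The cost is wording and a few degrees of freedom. In the simulations, adding the time-by-covariate term changed the SE by between about −2% and +2%. Recruitment is expected to end on 28 February 2027. The trial is open-label, so the deadline to state is the start of analysis, not an unblinding.
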